## 10.0 EVALUATION DURING TREATMENT/INTERVENTION

Please see study flow chart (**Appendix A**)

During the first 4 weeks of OSI-774 therapy, patients will be seen on a weekly basis (+/- 3 working days if the patient is unable to be seen for logistical reasons such as holidays, etc). Thereafter, doctor visits and labs, including CBC, electrolyte and chemistry profile with liver function tests, will be every 4 weeks until completion of treatment. CT scanning of all indicator lesions will be performed every 8 weeks in order to determine response to OSI-774 or progression of disease. Patients will undergo repeat ECG at the end of treatment. The Lung Cancer Symptom Scale (LCSS) will be administered at baseline and every week for the first five weeks. After the ninth week, the LCSS will be administered every 4 weeks until the end of study. The LCSS patient form requires a second grade reading level and takes an average of 8 minutes to initially administer, including instruction time. Once a patient has become familiar with filling it out, it takes only 3-5 minutes to complete. The LCSS is designed as a disease- and site-specific measure of quality of life with lung malignancies and their effect on overall symptomatic distress, functional activities, and global quality of life. The LCSS consists of two scales: one completed by the patient and an optional one for health care professionals ("counterpart observer") to provide context. Only the patient scale will be administered in this study. The nine-item patient scale includes nine visual analogue scales (100-mm horizontal line) where the patient puts a mark on a line to indicate intensity of response to the items in question (0 = lowest rating; 100 = highest rating). One LCSS sub-score is the average symptom burden index computed as the mean score for all six major symptoms (loss of appetite, fatigue, cough, dyspnea, hemoptysis, and pain). Time to symptomatic progression will be measured in terms of a worsening in this index.

[figure not shown]

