## 9.0 TREATMENT/INTERVENTION PLAN

All patients will receive OSI-774, 150 mg orally daily. During the fifth and ninth weeks of OSI-774, patients will undergo CT scanning to include all indicator lesions in order to detect a response to OSI-774 or progression of disease. CT scanning will be obtained every 8 weeks thereafter. Physical examination and laboratory assessment, including complete blood count and chemistry panel will be required every 8 weeks.. Should drug toxicity develop, dose delays and/or dose reductions will be carried out according to criteria outlined in Section 11.0. Patients will continue receiving OSI-774 until they refuse further therapy, develop evidence of progressive disease, unacceptable toxicity, or any condition, which would, in the judgment of the investigator, affect assessments of clinical status to a significant degree or would pose undue risk to the patient through continuation.

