**12.0 CRITERIA FOR THERAPEUTIC RESPONSE/OUT COME ASSESSMENT**

For the purposes of this study, patients will undergo repeat CT scanning of all indicator lesions following four and eight weeks of OSI-774 therapy. Thereafter, CT scanning will be obtained every eight weeks. See Appendix F for methods of response assessment and classification.

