## 14.0 BIOSTATISTICS

This will be a multicenter non-randomized single arm phase II trial seeking to determine whether OSI-774 results in a meaningful proportion of responses accompanied by symptomatic relief and improved quality of life in patients for whom no other standard therapy is available or commonly effective.

Patients will be asked to complete the Lung Cancer Symptom Scale at baseline and during the trial. Changes in the mean 100 mm visual analogue scale scores measuring disease-related symptoms for patients will be recorded weekly for the first four weeks of treatment and monthly thereafter. Nine symptoms (hemoptysis, pain, appetite, cough, dyspnea, activity, quality of life, fatigue, and lung cancer symptoms) will be recorded. Each patient's score on a given symptom will undergo square-root transformation to stabilize variance, followed by calculation of the difference from baseline to weeks 2, 3, 4, 5 and "best" timepoint. We have previously reported disease-related symptom improvement with this method [Miller, Cancer, 75(4), 1995].

A response rate of 15% or greater would be of interest in this patient population. An objective response rate of  $\geq 25\%$ , in conjunction with significant improvements in the LCSS may warrant consideration for regulatory submission. A complete response rate  $\geq 10\%$  would also warrant further study. A 2-stage design will be utilized. At the first stage, a total of 21 patients will be enrolled. If  $\geq 1$  response is noted, an additional 29 patients will be recruited to the second stage. This design assures that if no response is observed in the first 21 patients the likelihood of the true response rate being  $> 15\%$  is  $< 5\%$ . If  $\geq 12$  patients in the total sample of 50 patients demonstrate an objective response or  $\geq 5$  patients demonstrate a complete response, the sample size will be increased to 100 patients so as to provide better precision around the objective response rate and to generate additional safety and QOL data via the LCSS.

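### Sections 10 and 14 of the protocol disagree on the LCSS schedule in weeks 6 to 9, and Section 10 as written schedules no form at the week-9 CT

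*Protocol*

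**What the plan says.** Section 10 of the protocol: "The Lung Cancer Symptom Scale (LCSS) will be administered at baseline and every week for the first five weeks". The next instruction on timing is "After the ninth week, the LCSS will be administered every 4 weeks until the end of study". Nothing is stated for weeks 6 to 9.

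Section 14: changes in the LCSS scores "will be recorded weekly for the first four weeks of treatment and monthly thereafter". The planned analysis is the "calculation of the difference from baseline to weeks 2, 3, 4, 5 and" a best timepoint, on square-root-transformed scores.

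Tumour assessment, Section 9: "During the fifth and ninth weeks of OSI-774, patients will undergo CT scanning to include all indicator lesions". Section 12 describes the same scans as "patients will undergo repeat CT scanning of all indicator lesions following four and eight weeks of OSI-774 therapy".

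Three further provisions bear on the point. Section 10 defines time to symptomatic progression by a worsening of the average symptom burden index, which is computed from the LCSS. Section 13 takes a patient off study at progression. Section 14 says that a response rate of at least 25%, together with significant LCSS improvement, may justify considering a regulatory submission.

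**The concern.** The two sections give different instructions for the same questionnaire. A site that follows Section 10 as written collects nothing between the week-5 form and some point after week 9. A site that follows Section 14 collects a form about four weeks after the weekly series ends.

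The gap spans the second tumour assessment. Under Section 10 a patient whose week-9 CT shows progression leaves the study with week 5 as the last scheduled score. Any symptomatic change in the preceding four weeks goes unrecorded, and no later analysis can recover a questionnaire that was never given.

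Two analyses named in the protocol draw on scores after week 5: the best timepoint, which depends on which forms exist, and time to symptomatic progression, which depends on when a worsening can first be seen.

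**Working it through.** The protocol states no figure to reproduce. The check lists the form times that each section implies and sets them against the CT times.

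**Week convention.** Section 9 places the first two scans in the fifth and ninth weeks, and Section 12 places them after four and eight weeks of therapy. So a visit after *k* completed weeks falls in week *k* + 1.

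**Section 10.** Weekly forms run to week 5. The next form is due after week 9. The earliest literal reading is week 10. If the four-week interval is counted from week 9, the next form falls in week 9 + 4 = 13.
- Shortest gap: 10 − 5 = 5 weeks.
- Longest gap: 13 − 5 = 8 weeks.

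**Section 14.** Four weekly forms after baseline fall in weeks 2, 3, 4 and 5 on the convention above, and the first monthly form in week 5 + 4 = 9. If the weeks are instead counted 1 to 4, the first monthly form falls in week 4 + 4 = 8. The gap is 4 weeks either way.

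| | Last weekly form | Next form | Gap | Form at about the week-9 CT |
|---|---|---|---|---|
| Section 10 | week 5 | week 10 to 13 | 5 to 8 weeks | none stated |
| Section 14 | week 5 (or 4) | week 9 (or 8) | about 4 weeks | yes, by implication |

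**Effect on dating a worsening.** A worsening that begins just after the last weekly form is first recorded one full gap later: 5 to 8 weeks under Section 10, about 4 under Section 14. If onset is assumed uniform over the gap, the mean delay is half the gap: 5/2 = 2.5 to 8/2 = 4 weeks, against 4/2 = 2 weeks.

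**Effect on the fixed-week comparisons.** Weeks 2, 3, 4 and 5 are covered by Section 10, and by Section 14 on the convention above. These comparisons do not change.

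**The case against.** The strongest answer is that this is a dropped phrase and not a designed gap. Since 5 + 4 = 9, and four-weekly forms are then said to follow week 9, a week-9 form was probably intended. Section 10 opens by referring to the flow chart in Appendix A, which is not at hand and may list that form. Section 14 never names week 9; its form at about week 8 or 9 is an inference from the monthly interval. All of this stands, and it limits the finding to what the text of Section 10 states. It does not remove the disagreement between the two sections.

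It is also fair to say that no analysis in the protocol pairs a patient's CT with a same-week LCSS score, that time to symptomatic progression is not among the Section 2 objectives, and that the loss of later scores after progression comes mainly from Section 13 and would occur after week 9 under either schedule. These points keep the finding small.

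A reader might draw three stronger conclusions that the document does not support:
- **That Section 14 analyses a week-5 change it does not collect.** Four weekly forms after baseline fall in weeks 2 to 5 on the protocol's own convention, so four against five weeks is most likely a difference in counting.
- **That a large share of patients would leave by week 9**, judging from the progression figures for the earlier NSCLC study in Section 3. That study's summary gives no progression times, and its patients were platinum-pretreated and selected for EGFR expression, a different population.
- **That the shift in the best-timepoint value can be sized** by comparing the expected maximum of independent scores. Repeated scores in one patient are correlated, and the protocol gives no correlation.

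**Conclusion.** The point holds as a minor inconsistency. As written, Section 10 leaves 5 to 8 weeks without an LCSS form, against about 4 under Section 14. The 8-week figure is the upper end and applies only if the first later form falls in week 13. A patient who comes off study for progression at the week-9 CT has no scheduled score after week 5 under Section 10, and a worsening in weeks 6 to 9 is dated to week 10 or later.

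The number of patients affected cannot be given. It depends on how many leave between the two scans or at the second, and the protocol has no figure for that.

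The conclusion rests on a literal reading of Section 10, on taking monthly in Section 14 as about four weeks, and on the absence of Appendix A. If the flow chart lists a week-9 form, what remains is a wording correction. The matter cannot be left to a statistical analysis plan, because it concerns which data are collected.

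**What to change.** State one LCSS schedule, use it in Sections 10 and 14, and check it against Appendix A: baseline, weeks 2, 3, 4, 5 and 9, then every 4 weeks until the end of study. This covers every fixed analysis week and puts a form at both early CT assessments.

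The cost is an amendment to one sentence in each section and, relative to Section 10 as written, one extra form per patient. Section 10 puts a repeat form at 3 to 5 minutes, and the visit already takes place: doctor visits are four-weekly after the first four weeks, and the CT falls in week 9.

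A form at the off-study visit could be added, but it is optional and not needed to resolve the conflict.

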## 11.0 TOXICITIES/SIDE EFFECTS

NCI Common Toxicity Criteria (CTC): This study will utilize the Common Toxicity Criteria (CTC) version 2.0 for toxicity and Adverse Event reporting. A copy of the CTC version 2.0 can be downloaded from the CTEP home page (<http://ctep.info.nih.gov>). All treatment areas have access to a copy of the CTC version 2.0.

All toxic effects will be managed symptomatically, as indicated. Toxicities will be graded using the NCI Common Toxicity Criteria. Dose adjustments will be made as follows:

Dose reduction or interruption of study drug for adverse events may take place at any time during the study. Toxicity is based on NCI-CTC, Version 2.

Management of Grade 1 or 2 rash should include continuation of study drug at the current dose and symptomatic management. If skin rash persists or worsens over 10–14 days, dose reduction according to Table 2 should be considered. Management of Grade 3 rash should include dose reduction and symptomatic management. When skin toxicity improves by at least one grade level, the dose may be re-escalated as tolerated. In Phase II trials, this approach enabled dose re-escalation for the majority of patients requiring dose reduction for skin toxicity. Patients experiencing Grade 4 skin toxicity should be discontinued from the study.

For Grade 1 or 2 diarrhea, early intervention should include continuation of study drug at the current dose and initiation of loperamide therapy as described in **Table 3**. Persistent Grade 2 diarrhea, despite optimal medical management over 48–72 hours, should be managed by dose reduction according to **Table 2**. Patients should be maintained at the reduced dose without attempt at dose re-escalation. Patients experiencing Grade 3 diarrhea should interrupt study drug until resolution to Grade  $\leq 1$  and restart at a reduced dose according to **Table 2**. Patients experiencing Grade 4 diarrhea should be discontinued from the study.

Patients who experience Grade 3 fatigue should be managed with a dose reduction of 150mg to 100mg. Patients who experience Grade 4 fatigue should be discontinued from study.

Other serious adverse events or Grade 3 or 4 adverse events considered to be related to study drug should be managed with dose interruption until resolution of the event (Grade  $\leq 1$ ). Other serious adverse events or Grade 3 or 4 adverse events not resolving in 2 weeks will result in patient discontinuation. Patients may be rechallenged with study drug at the same dose level if the criteria for rechallenge are met. If the adverse event recurs after rechallenge, the patient should be withdrawn from the study.

[figure not shown]

Memorial Sloan-Kettering Cancer Center  
IRB Protocol

IRB#: 02-010A(8)

Interstitial lung disease/pneumonitis associated with increasing shortness of breath with exertion or at rest may occur. Patients should be instructed to stop drug immediately if they note a worsening of baseline dyspnea or if they develop dyspnea while taking Tarceva. The attending physician should be instructed to immediately start steroids (1 mg/kg) once an infectious etiology has been satisfactorily excluded and to continue steroid treatment for several weeks with a gradual taper as appropriate to maintain optimal pulmonary function.

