**Table 2: OSI-774 Dose Level Reductions**

| Starting Dose | First Reduction | Second Reduction |
|---------------|-----------------|------------------|
| 150 mg/day    | 100 mg/day      | 50 mg/day        |

Within 2 weeks following a dose interruption or reduction, study drug-related toxicity must improve by at least one grade and be Grade  $\leq 1$ , or further dose reduction by one level will be required. Dosing may be interrupted for a maximum of 2 weeks if clinically indicated and if the toxicity is not controlled by optimal supportive medication. No more than two dose reductions will be allowed.

**Table 3** outlines study drug dose modification criteria for study drug-related toxicities as well as guidelines for their management.

[figure not shown]

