**Table 3: Dosage Modification Criteria and Guidelines for Management of Study Drug-Related Toxicities**

| Toxicity,
NCI-CTC Grade       | Study Drug Dose
Modification                                      | Guideline for Management                                                                                                                                                                               |
|----------------------------------|----------------------------------------------------------------------|--------------------------------------------------------------------------------------------------------------------------------------------------------------------------------------------------------|
| Diarrhea                  |                                                                      |                                                                                                                                                                                                        |
| Grade 1                          | None                                                                 | Consider loperamide (4 mg at first onset, followed by 2 mg q 2–4 hours until diarrhea free for 12 hours)                                                                                               |
| Grade 2                          | None                                                                 | Loperamide (4 mg at first onset, followed by 2 mg q 2–4 hours until diarrhea free for 12 hours)                                                                                                        |
| Grade 3                          | Interrupt                                                            | Interrupt until resolution to Grade $\leq 1$ , and restart at reduced dose                                                                                                                             |
| Grade 4                          | Discontinue study                                                    |                                                                                                                                                                                                        |

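### Section 11.0 gives conflicting instructions for toxicity still unresolved two weeks after a dose interruption, and its discontinuation sentence omits the limit to drug-related events

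*Protocol*

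**What the plan says.** Protocol Section 11.0 gives separate rules for rash, diarrhea and fatigue, then a rule for other events, then a general rule under Table 2.

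- **Other events, interruption.** "Other serious adverse events or Grade 3 or 4 adverse events considered to be related to study drug should be managed with dose interruption" until the event is at Grade ≤1. This sentence is limited to drug-related events.
- **Other events, at two weeks.** The next sentence reads: "Other serious adverse events or Grade 3 or 4 adverse events not resolving in 2 weeks will result in patient discontinuation". It carries no such limit. Rechallenge at an unchanged dose is allowed on certain criteria; no reduction step is mentioned.
- **Grade 3 diarrhea.** "Patients experiencing Grade 3 diarrhea should interrupt study drug until resolution to Grade" ≤1, then restart at a reduced dose. Table 3 repeats this: "Interrupt until resolution to Grade" ≤1, then restart lower. Neither place gives a time limit.
- **General rule under Table 2.** "Within 2 weeks following a dose interruption or reduction, study drug-related toxicity must improve by at least one grade and be Grade" ≤1, "or further dose reduction by one level will be required. Dosing may be interrupted for a maximum of 2 weeks". The two-week maximum applies where an interruption is clinically indicated and supportive medication has not controlled the toxicity.

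**The concern.** An investigator with a patient whose toxicity has not settled after two weeks off drug needs one instruction. Section 11.0 gives more than one. For one class of event the choice is between ending treatment and continuing at a lower dose. For Grade 3 diarrhea it is between holding drug and ending the hold. The protocol describes diarrhea as the only dose-limiting toxicity seen to date, so the second case concerns the drug's main known risk.

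Section 15.1 has five institutions registering patients. If sites follow different sentences, patients with the same event will have different drug exposure, and discontinuation counts and time on treatment will partly reflect which sentence was read. There is also a question of reach: the discontinuation sentence does not say that it applies only to events caused by the drug.

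**Working it through.** No arithmetic applies. The check sets the instructions side by side for three cases.

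**Case 1: a drug-related Grade 3 event other than rash, diarrhea or fatigue; drug interrupted; event still Grade 2 at two weeks.**

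| Source | Clock | Threshold | Consequence |
|---|---|---|---|
| Section 11.0, other events | 2 weeks | Grade ≤1 (how the preceding sentence defines resolution) | Patient discontinued |
| Section 11.0, text under Table 2 | 2 weeks after interruption or reduction | At least one grade better and Grade ≤1 | "or further dose reduction by one level will be required" |

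Clock and threshold are the same, and both consequences are mandatory. The general rule names interruption as well as reduction and covers drug-related toxicity without restriction by type, so this event falls under both. The result does not depend on how Grade 2 is classed: an event still at Grade 3 is unresolved on any reading and meets the same two consequences.

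**Case 2: Grade 3 diarrhea; drug interrupted; diarrhea at Grade 2 on day 14.**

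- Section 11.0 and Table 3: the condition for restarting (Grade ≤1) is not met, so drug stays off.
- Text under Table 2: the longest permitted interruption has been reached, and because Grade ≤1 was not reached, a one-level reduction is required.

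The first makes restarting wait for Grade ≤1. The second ends the waiting at two weeks. A patient above Grade ≤1 at that point cannot remain on treatment and satisfy both. Taking the patient off treatment would breach neither the hold nor the cap, but no sentence says to do so for Grade 3 diarrhea, and a required reduction presupposes that treatment continues.

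**Case 3: a serious or Grade 3–4 event judged unrelated to the drug and lasting more than two weeks.**

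- Interruption sentence: does not apply, because it covers only events "considered to be related to study drug should be managed with dose interruption until resolution of the event".
- Discontinuation sentence: applies as written, because it repeats the opening of the interruption sentence without that limit.

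Section 13.0 does not settle any of the three. It removes patients for unacceptable toxicity or on investigator judgment and sets no two-week rule.

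**The case against.** The strongest reply is that a specific rule governs a general one. The paragraph on other events is specific and has its own path (interrupt, rechallenge at the same dose, or discontinue) with no reduction step. The text under Table 2 speaks of a further reduction, which fits patients already on the reduction ladder. This is a reasonable way to choose between the two, but the protocol does not state it, and the general rule's explicit mention of interruption works against it. The conflict in Case 1 stands.

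On diarrhea, it can be said that a specific instruction silent on duration and a general cap are meant to be read together, and that both lead to a lower dose. That works for a patient who reaches Grade ≤1 within two weeks. It fails for one who does not, which is the case at issue.

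On relatedness, the context favors the narrower reading. The sentence continues the one before it, and both the general rule and the title of Table 3 refer to drug-related toxicity. Much of this stands: the wide reading is a literal one, and the defect is an omitted qualifier rather than an evident intention to remove patients for unrelated events.

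A reader might infer that one patient can be discontinued, reduced or held, depending on the sentence read. The documents do not support that. Discontinuation and reduction meet only for other drug-related events; holding and reduction meet only for Grade 3 diarrhea. No single toxicity carries all three outcomes, and no such conflict is shown for rash or fatigue.

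**Conclusion.** The concern holds in three limited parts: opposed mandatory instructions for drug-related other events at two weeks; instructions for Grade 3 diarrhea that cannot both be followed if Grade ≤1 has not been reached by day 14; and a discontinuation sentence whose reach is unclear. The consequence is mainly for patient safety and consistency between sites.

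A reader might go on to put a size on the primary endpoint. Section 14.0 expands the trial at 12 or more responses in 50, and losing one would-be responder acts like moving that trigger to 13. With X binomial (50, p), P(X ≥ 12) against P(X ≥ 13) is 0.618 against 0.489 at p = 0.25, and 0.289 against 0.186 at p = 0.20. The arithmetic is right, but it does not measure this defect:

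- It assumes that exactly one responder is lost because of this wording, and nothing in the protocol gives a frequency for that.
- In the 56-patient NSCLC study at 150 mg/day summarized in Section 3.0, no patient stopped drug for a drug-related event.
- A patient already in response at the four-week scan need not be lost to the count.
- Section 14.0 also allows expansion on 5 or more complete responses, which the calculation ignores.

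No size of effect on the response count can therefore be derived from the documents. The finding rests on the current wording alone and takes no view on which clinical rule is right.

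**What to change.** Amend Section 11.0 so that its toxicity paragraphs, the text under Table 2 and Table 3 agree:

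1. For other events, give one instruction for what happens when the event is not at Grade ≤1 two weeks after interruption, and say whether the general rule under Table 2 applies to them.
2. For Grade 3 diarrhea, give one instruction for what happens when Grade ≤1 has not been reached at two weeks, worded alike in the text and Table 3.
3. State whether the discontinuation sentence is limited to drug-related events, as the sentence before it is.

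The clinical team chooses the rule in each case; the requirement here is only that the passages be reconciled. The cost is amendment wording in one section, with no additional patients, visits or procedures.
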